#### Primary efficacy analyses

As we expect a quantitative interaction regarding the DGF (primary outcome) between the preservation solution (with or without HEMO_2_life®) and the types of preservation (either in cold storage or on machine perfusion), we decided to incorporate this information into the confirmatory testing strategy. This implementation will allow the investigator to make inferences on the overall population and/or on a prespecified subgroup (cold storage). The methodology developed by Alosh and Huque [31] requires first testing the global efficacy at a reduced alpha level α0. Based on this result and on a consistency constraint within the complementary subgroup (machine perfusion), the efficacy for the cold storage subgroup may also be tested. The flowchart below (Fig. 2) depicts the entire confirmatory testing strategy (where p stands for the p value in the total patient population, ps stands for the p value in the prespecified subgroup, being cold storage, and α is the familywise error rate), with the choice of α = 0.03.

**Fig. 2 Fig2:**
[figure not shown]
The flowchart depicts the entire confirmatory testing strategy. This implementation will allow the investigator to make inferences on the overall population and/or on a prespecified subgroup (cold storage). The methodology developed by Alosh and Huque [31], which requires meeting some consistency constraints as a prerequisite for testing the next hypothesis, will be used. This proposed methodology requires first testing global efficacy at a reduced alpha level α0. Based on this result and on a consistency constraint within the complementary subgroup (machine perfusion), the efficacy for the cold storage subgroup may also be tested. The variability (standard deviation) is assumed to be similar in the two subgroups. Therefore, the significance level for the subgroup of interest α*S* is derived from the proportions of the subgroups, which are expected to be balanced within the global sample, i.e., 50% cold storage and 50% machine perfusion. This yields an α*S* equal to 0.02633 (two-sided) to control for the familywise error rate (FWER) strongly

The full analysis set (FAS) will be used to perform the primary efficacy analyses. McNemar's test will be used to compare paired proportions (DGF) between patients receiving a kidney preserved with HEMO_2_life® and those receiving a kidney preserved without HEMO_2_life®.

#### Safety analyses

Adverse events will be described using the Preferred Terms (PT) of the MedDRA Hierarchy. The chi-square test or Fisher’s exact test will be used to compare proportions between the two groups.

### Interim analyses {21b}

Not applicable, no interim analysis planned.

### Methods for additional analyses (e.g. subgroup analyses) {20b}

Not applicable, no additional analysis planned.

### Methods in analysis to handle protocol non-adherence and any statistical methods to handle missing data {20c}

#### Missing data

No missing data of the primary outcome are expected except for early (first week) deceased patients. For them, the primary outcome will be imputed as a failure (as a requirement for dialysis during the first week after transplantation).

### Plans to give access to the full protocol, participant level-data and statistical code {31c}

As French law, the datasets generated and/or analyzed during the current study are not publicly available but are available for scientific purpose from the corresponding author on reasonable request after the agreement of the sponsor and the ethics and steering committees.

## Oversight and monitoring

### Composition of the coordinating centre and trial steering committee {5d}

A steering committee has been formed, composed of the principal investigator of each participating center from the first line. It will be responsible for the smooth conduct of the study. It will discuss needed changes to the protocol and will analyze safety reports and alerts prepared by the sponsor or the Independent Data and Safety Monitoring Board composed of three independent experts (IDSMB).

### Composition of the data monitoring committee, its role and reporting structure {21a}

The data will be monitored by an IDSMB of three independent experts in the field of kidney transplantation. The role of the DSMB is to monitor the data from published clinical research that affect patient safety and to ensure that the risk/benefit balance is maintained. Safety reports after the first 25, 75 and 150 pair grafts that have reached the first week after transplantation will be transmitted to the DSMB by the sponsor. This document will be issued within a month by the sponsor safety department and will gather all reported SAEs and AEs, as well as a summary of the incidents/events of interest that occurred during surgeries. A meeting of the IDSMB will be held immediately, and the IDSMB will have to give its recommendation to the steering committee no later than one week after: continuation of study without protocol modification, modification of protocol to improve patient security, and early termination.

### Adverse event reporting and harms {22}

SPIRIT guidance: Plans for collecting, assessing, reporting, and managing solicited and spontaneously reported adverse events and other unintended effects of trial interventions or trial conduct. All adverse events, even unrelated to HEMO2life® occurring during the first month, serious adverse event occurring during the 12 months after transplantation or adverse effect with no time limit will be collected in the study database. When the investigator evaluates the AE as abiding the definition of serious AE, he/she will declare it to the safety Department of the Brest University Hospital. The sponsor must establish once a year during the duration of the clinical trial or on request, an Annual Security Report (ASR) on the clinical trial concerned. He must send it to Agence Nationale de Sécurité du Médicament (ANSM) and Ethic Committee. Its objective is to describe concisely any new information relevant to the safety and assess the safety of persons participating in this Clinical trial.

### Frequency and plans for auditing trial conduct {23}

The trial will be supervised by the sponsor. Research assistants from Brest University Hospital will regularly perform on-site checks of adherence to the protocol and accuracy of the recorded data. Newsletters will be regularly sent to all participants to provide support, information and to recall key instructions. Safety reports after the first 25, 75 and 150 pair grafts will be transmitted to the DSMB by the sponsor. A meeting of the IDSMB will be held immediately, and the IDSMB will have to give its recommendation to the steering committee no later than one week after.

### Plans for communicating important protocol amendments to relevant parties (e.g. trial participants, ethical committees) {25}

The sponsor’s approval is required, in case of any substantial modification applied to the protocol by the investigator. Prior to the trial implementation, the sponsor will be in charge of obtaining the Ethic Committee approval and the regulatory authorization within their respective framework. These modifications will be notified to the participating centers.

### Dissemination plans {31a}

Communications and scientific reports about the study will be elaborated under the principal investigator’s responsibility after co-investigators’ approval. All actors who have contributed substantially in study design, data collection, data analysis and interpretation, manuscript preparation and critical revising, and in final manuscript version approval, will be affiliated as authors. The sponsor and funders will be acknowledged in the published manuscript. Publishing rules will follow the international recommendations (N Engl J Med, 1997; 336(4):309–15).

## Discussion

The use of HEMO_2_life® in preservation solutions is a novel approach, allowing for the first time the delivery of oxygen to organs in storage. Preclinical studies in different animal models have suggested the perfect safety of the molecule and its beneficial effect on ischemia‒reperfusion phenomena [24, 25]. Clinical HEMO_2_life® tolerance in humans was evaluated in our previous safety study [26, 27]. Therefore, the present randomized controlled trial is necessary to assess the efficacy of the product, particularly in specific populations of donors: ECD and DCD. Additionally, it will be of great interest to evaluate the combination of machine perfusion plus HEMO_2_life®. The opportunity is due to this breakthrough oxygen carrier, HEMO_2_life®, and its ability to reduce lesions induced by hypoxia is of major interest. Improving graft survival by limiting these lesions is a major goal of public health in the field of organ transplantation. Its use for the preservation of other organs, particularly for those prone to IRI, such as hearts and lungs, is also expected.

## Trial status

Due to the Covid pandemia the inclusions that were supposed to start in February 2020 were delayed and the recruitment was difficult until end of 2020. The uncertainty regarding the recruitment and the risk of withdrawal of the study explain that we did not submit the manuscript before. Finally, we included the last patient in July 2022. A total of 520 patients were finally included to obtain the 160 pairs needed for analysis. The last one-year visit of the last patient is scheduled in July 2023.

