## Interventions

### Explanation for the choice of comparators {6b}

The two kidneys coming from one donor will be randomly allocated: one to the standard-of-care arm (organ preserved in preservation solution routinely used according to the local practice) and the other to the active treatment arm (HEMO_2_life® on top of routinely used preservation solution).

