### Sample size {14}

This sample size is based on the confirmatory testing strategy described below, according to Alosh and Huque’s methodology [31]. This methodology allows us to make inferences on the overall population and/or on a prespecified subgroup (graft preserved in cold storage) while controlling for the familywise error rate (FWER).

This proposed methodology requires first testing global efficacy at a reduced alpha level, chosen here to be 0.03. In the 3 cumulating years 2015 to 2018 the mean rate of DGF in France was 28% according to the data of Agence de la Biomédecine (https://rams-archives2019.agence-biomedecine.fr/sites/default/files/2021-01/LE%20RAPPORT%20M%C3%89DICAL%20ET%20SCIENTIFIQUE%20DU%20PR%C3%89L%C3%88VEMENT%20ET%20DE%20LA%20GREFFE%20EN%20FRANCE2.zip). The sample size calculation rests on an expected DGF rate of 28% in the control arm and a 15% rate in the HEMO_2_life® arm. To guarantee 80% power to detect such a difference at this first step, the minimum sample size per group is 180 evaluable grafts. Expecting 20% of nonevaluable inclusions, a total of 450 patients (225 pairs) are needed.

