### Recruitment {15}

We anticipate 10 to 15% of preemptive grafts in the protocol. These kidneys will not be analyzed in the paired analysis for the primary endpoint because they are less likely to require hemodialysis. Therefore, enrollment will be continued until the required sample size in terms of evaluable paired kidneys (180 pairs) is achieved. In total, we expect to include approximately 260 donors in the study.

Nonevaluable inclusions include discordant pairs according to the type of conservation (cold storage/perfusion machine) as well as nontransplanted grafts.

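### Trial status gives 160 pairs as the number needed, while the sample size and recruitment sections require 180 evaluable pairs; the two must be reconciled, and if 160 is real the stated 80% power has to be restated

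*Protocol article*

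**What the plan says.** The protocol article fixes the target in two places and reports a different number in a third.

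- **Sample size {14}:** the basis is an "expected DGF rate of 28% in the control arm and a 15% rate" in the HEMO2life arm. The level is given by "This proposed methodology requires first testing global efficacy at a reduced alpha level, chosen here to be 0.03". The result is "To guarantee 80% power to detect such a difference at this first step, the minimum sample size per group is 180 evaluable grafts". Allowing for losses: "Expecting 20% of nonevaluable inclusions, a total of 450 patients (225 pairs) are needed".
- **Recruitment {15}:** because preemptive grafts drop out of the paired analysis, "enrollment will be continued until the required sample size in terms of evaluable paired kidneys (180 pairs) is achieved". The section expects about 260 donors for this.
- **Trial status:** the last patient was included in July 2022, and "A total of 520 patients were finally included to obtain the 160 pairs needed for analysis".

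The Interim analyses section plans none, and no section describes a re-estimation or a change of target.

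**The concern.** The article describes 160 pairs as what the analysis required, but the only requirement it states is 180. One of the two statements is wrong, or the target was changed without saying so.

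If 160 is the real count, the rule for ending enrolment was not followed, and the 80% power attached to the confirmatory first step no longer describes the trial on the basis the plan used. A reader weighing a non-significant first step would then start from a power figure calculated for a larger sample. If 160 is a slip, the status paragraph misreports the size of the primary analysis set. Either way the text needs a correction.

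**Working it through.** **Inputs.** DGF rates p1 = 0.28 and p2 = 0.15, so d = 0.13; first-step level 0.03; power 80% (all from Sample size). One kidney of each donor goes to each arm (Explanation for the choice of comparators: "The two kidneys coming from one donor will be randomly allocated: one to the standard-of-care arm"), so grafts per group equals pairs. Sidedness is not stated for 0.03. I take it as two-sided because the subgroup level is given as "equal to 0.02633 (two-sided") and because only the two-sided version reproduces 180. Normal quantiles: z(0.985) = 2.170, z(0.80) = 0.842.

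**Step 1: reproduce the plan's 180.** Pooled two-proportion formula, no continuity correction, with mean rate 0.215:

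n = [2.170 × √(2 × 0.215 × 0.785) + 0.842 × √(0.28 × 0.72 + 0.15 × 0.85)]² / 0.13²

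= [2.170 × 0.5810 + 0.842 × 0.5737]² / 0.0169 = 179.9, that is 180.

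Then 180 / 0.80 = 225 pairs, or 450 patients. Both stated figures are reproduced.

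**Step 2: power of the same formula at 160.**

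z = (0.13 × √160 − 2.170 × 0.5810) / 0.5737 = (1.644 − 1.261) / 0.5737 = 0.669, so power is 74.8%.

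At 180 the same expression gives 80.0%. The loss is 5.2 percentage points for 20 pairs (20/180 = 11%).

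**Step 3: the planned test, McNemar.** Let ρ be the within-pair correlation of DGF, which is an assumption because the article states none. The probability that both kidneys of a donor have DGF is p11 = 0.28 × 0.15 + ρ√(0.28 × 0.72 × 0.15 × 0.85) = 0.042 + 0.1603ρ. The discordant probabilities are b = 0.28 − p11 and c = 0.15 − p11. With ψ = b + c,

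power = Φ{[d√n − 2.170√ψ] / √(ψ − d²)}.

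| ρ (assumed) | b, c | Pairs for 80% | Power, 160 pairs | Power, 180 pairs |
|---|---|---|---|---|
| 0 | 0.238, 0.108 | 183.1 | 73.9% | 79.3% |
| 0.1 | 0.222, 0.092 | 165.9 | 78.4% | 83.4% |
| 0.2 | 0.206, 0.076 | 148.7 | 83.1% | 87.5% |
| 0.3 | 0.190, 0.060 | 131.5 | 87.7% | 91.4% |

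Interpolating between the first two rows, 160 pairs reach 80% at ρ ≈ 0.1 × (183.1 − 160) / (183.1 − 165.9) = 0.13.

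These are normal approximations. Full enumeration of the uncorrected test at 160 pairs gives 75.1%, 79.6% and 84.3% at ρ = 0, 0.1 and 0.2. The exact version of the test gives 70.2%, 75.4% and 80.8%.

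**Step 4: does any stated basis lead to 160?** At 0.03, the two-sided formula with continuity correction gives 195, the one-sided formula 147, and the one-sided formula with correction 162. At two-sided 0.05 it gives 156, with 81.1% power at 160. None of these gives 160, and none is the basis the article describes.

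**Step 5: the enrolment figures.** With two recipients per donor, 520 patients is 260 donors, the number the Recruitment section expected in order to reach 180 pairs. The 260 is consistent with 225 pairs and 10 to 15% preemptive grafts: 225/0.90 = 250 and 225/0.85 = 265 (my reconstruction). A true 160 means a yield of 160/260 = 61.5%, against 180/260 = 69.2% expected.

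**The case against.** **The figure may be a slip.** The status sentence is worded as a requirement that was met, the only stated requirement is 180, and 520 patients matches the 260 donors planned for 180 pairs. That is a fair case, and a reader who infers that the trial certainly stopped short goes further than the article allows. A real shortfall is equally possible: the same paragraph reports recruitment trouble during the pandemic, and a lower yield from the planned number of donors would explain 160. The article does not settle it, so the correction has to be conditional.

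**Pairing may make up the loss.** The 180 comes from a formula for independent groups, but the analysis is paired. Positive correlation between the kidneys of one donor raises the power of McNemar's test, and about 0.13 would bring 160 pairs back to 80%. This stands. Actual power at 160 could lie on either side of 80%, so one cannot say that the trial lacked adequate power, only that the stated 80% does not follow from the stated basis. The article gives no correlation or discordance rate to support the paired argument.

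**A move to 0.05.** Because 160 lies close to what two-sided 0.05 requires, a reader might infer that the overall test was quietly moved to 0.05 and that the familywise error is inflated. The documents do not support this. The testing strategy sets the overall test at 0.03, and nothing mentions another level. The cold-storage test is also conditional on a consistency constraint in the machine-perfusion subgroup, so a calculation that ignores the constraint would overstate any inflation. The threshold is not in the available text.

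**Conclusion.** The point holds as an unreconciled contradiction: 180 evaluable pairs required in two sections, 160 called needed in a third, and no revision of the target anywhere.

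If 160 is real, first-step power for 28% versus 15% at two-sided 0.03 is about 75% on the plan's own basis rather than 80%, so the chance of missing the assumed effect rises from about 20% to about 25%. That rests on the stated DGF rates and on treating the two kidneys of a donor as independent. With within-pair correlation, power at 160 runs from about 74% (none) to 83% (0.2). If 160 is an error, the power statement is untouched and only the status sentence is wrong.

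The primary test, the analysis population and the type I error are not affected. This should be fixed, but it does not threaten the validity of the trial.

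**What to change.** Confirm the number of evaluable pairs from the trial data, then do one of two things.

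- **If 160 is an error:** correct it in Trial status to the true number.
- **If 160 is correct:** replace the claim that 160 were needed with *160 evaluable pairs obtained against 180 planned*, and give the reason enrolment closed below the target. Restate first-step power for 28% versus 15% at two-sided 0.03 as about 75% on the independent-proportions basis, and add the McNemar values of about 74%, 78% and 83% at assumed within-pair correlations of 0, 0.1 and 0.2. Say that 80% is reached only from about 0.13 upward and that the plan specified no correlation. State that the first-step test stays at 0.03.

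The cost is a few sentences. No new patients are needed and no analysis changes. In the second case the reported power becomes less favourable.

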## Data Availability

Any data required to support the protocol can be supplied on request.

## Abbreviations

AE: Adverse Event
CRA: Clinical Research Assistant
CRF: Case Report Form
DBD: Donor after Brain Death
DCD: Deceased Donor
DGF: Delayed Graft Function
DSMB: Data and Safety Monitoring Board
ECD: Extended-Criteria Donor
eCRF: Electronic Case Report Form
eGFR: Estimated Glomerular Filtration Rate
FAS: Full Analysis Set
FWER: Familywise Error Rate
HMP: Hypothermic Machine Perfusion
HTK: Histidine-Tryptophan-Ketoglutarate
IDSMB: Independent Data and Safety Monitoring Board
IRI: Ischemia‒Reperfusion Injury
PNF: Primary Non Function
QC: Quality Control
SCS: Static Cold Storage
UW: University of Wisconsin
